### Measures to assess participant-level clinical outcomes

Although clinical outcomes in this feasibility trial are secondary to the feasibility outcomes, we plan to collect data on our planned outcomes for a future trial to establish the feasibility of using the proposed measures. Measures will be considered feasible if fewer than 15% of items are incomplete (see Table 2).

### Proposed primary trial outcome measures

All primary outcomes are at the level of the individual patient and will be collected at baseline and at the two follow-up assessments (see Fig. 3).

#### Percent of heavy drinking days in the past month

We will use the Alcohol Timeline Follow Back (TLFB) technique to collect self-reported frequency, quantity, volume, patterns, and types of alcohol consumption. This will be used to calculate the percent of heavy drinking days (> 60 g absolute alcohol) in the past month [42].

#### Alcohol severity

Alcohol use will be measured using Alcohol, Smoking and Substance Use Involvement Test - youth (ASSIST-Y) scores [34]. The ASSIST-Y for adolescents aged 15–17 will be used. This measure categorizes people into low, moderate, or high risk for substance-related problems. Those with alcohol scores < 5 are considered low risk, ≥ 5 and ≤ 17 are considered at moderate risk, and ≥ 18 are considered high risk. This outcome is restricted to adolescents who report alcohol problems at baseline.

#### Symptoms of depression

We will use the Center for Epidemiologic Studies Depression Scale (CES-D-10), a 10-item scale that measures depressive feelings and behaviors during the past week to assess change in symptom severity on this outcome. This outcome is restricted to those with CES-D > = 10 at baseline. The CES-D 10 has been validated for use in South Africa and with adolescents [43, 44] and has shown good psychometric properties. A cut-off score of 10 indicates risk of depression, with scores ranging from 0 to 30 [45].

### Secondary outcome measures

#### Coping and problem-solving

Social problem-solving will be assessed using the Social Problem-Solving Inventory - Adolescent version, short form (SPSI-A, [46]. The SPSI-A SF consists of 30 items organized into three scales: Automatic Process, Problem Orientation, and Problem-Solving Skills.

#### Tobacco and other drug use

We will use the ASSIST-Y [34] to assess use of tobacco and other drugs. The ASSIST-Y collects information on frequency of tobacco and other drug as well as severity of risk for tobacco and other drug-related problems.

#### Anxiety

We will use the generalized disorder scale (GAD-7) to assess the severity of self-reported symptoms of generalized anxiety. The scale has been shown to have good psychometric properties [47, 48].

#### Family relationships

We will use the 10-item Family Involvement subscale of the Behavioral and Emotional Rating scale to assess the adolescent’s relationship with their family [49, 50].

#### Self-esteem

This will be measured using the 8-item Global Self Worth subscale of the Self Esteem Questionnaire [51]. This sub-scale has demonstrated high validity and adequate psychometric properties in South African adolescents [52].

#### Social support

The Multi-Dimensional Scale of Perceived Social Support (MSPSS) [53] will be used to assess social support from family, friends and significant others. This instrument has been shown to have good concurrent, construct and discriminant validity, and high internal and test re-test reliability [53] and good reliability and validity with adolescents [54].

#### School involvement

We will use the School Functioning subscale (9 items) of the Behavioral and Emotional Rating Scale (BERS) to assess the adolescents’ performance and competence in school. This scale assesses aspects such as attention in class and completion of school tasks [50].

### Sample size considerations

As we are not testing effect sizes in this feasibility trial, a power calculation is not required. Recommendations for sample size requirements to estimate key design parameters from external feasibility and pilot randomized controlled trials suggest that at least 70 measured subjects (35 per group) are required when estimating the SD for a continuous outcome [55]. Therefore, we will recruit 100 participants (50 per group) to account for attrition.

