### Participants

To be eligible for inclusion in this study, participants must (1) be aged between 15 and 18 years old; (2) provide written informed assent/consent to participate in the study; (3) have written informed parental consent to participate if younger than 18 years of age; (4) screen at risk for depression with a score ≥ 10 on the Center for Epidemiology Studies Depression Scale short form (CES-D-10 [33];) and/or screen at moderate or severe risk for alcohol-related health problems, with a score ≥ 5 on the Alcohol, Smoking and Substance Use Involvement Test-Youth (ASSIST-Y [34]); and report at least 2 episodes of heavy drinking (≥ 5 standard drinks on a single occasion) in the last month. Participants will be excluded if they are currently receiving any form of treatment for a mental or substance use disorder.

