### Data analysis

The quantitative outcomes of interest (see Table 2) will be summarized descriptively using appropriate summary statistics (mean and standard deviation for continuous outcomes and numbers and proportions for categorical outcomes) and presented graphically over time for both study arms.

We will explore clinical outcomes. In these exploratory analyses, we will calculate means and confidence intervals of clinical outcomes (both within- and between-study groups) and determine which outcomes are most sensitive to change. We will evaluate the parameters required to inform the sample size calculation for a future main trial. We will also assess change in clinical outcomes using an intention-to-treat analysis. Outcomes will be compared between intervention and control groups using linear regression models, adjusting for the baseline score of the given outcome. We will create separate models for alcohol and depression and only include participants who screen at risk at baseline. The two primary outcomes will be ascertained at three time-points for each participant. This repeated measure feature will be used to estimate the intervention effects and 95% confidence intervals for the two primary outcomes at 6 weeks and 3 months for the contrast between the intervention and comparison condition.

Qualitative data will be coded with NVivo and analyzed using the framework approach [56]. Transcripts of interviews will be read for emergent themes and then coded. Coding and analysis will continue iteratively. Two project staff will code the transcripts; they will meet after the first five transcripts, and thereafter after every 10 transcripts, to compare notes. Cohen’s Kappa will be used to measure inter-coder agreement. Following the Consolidated Criteria for Reporting Qualitative Studies (COREQ), we will document the process according to the 32-item checklist [57].

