Third, the proposed feasibility trial using a mixed-methods design will allow us to determine whether we can move forward to a larger effectiveness trial of the ASPIRE intervention. If our pre-specified qualitative or quantitative indicators highlight concerns regarding feasibility and acceptability impacting recruitment, retention, intervention delivery, data collection, randomization, blinding or safety, those relevant procedures will be modified accordingly. Should we find that significant modifications are required, we will consider the need for an internal pilot in the context of the full trial [66].

Despite these contributions and strengths of the proposed study, we anticipate some challenges to certain aspects of trial implementation. Recruitment of individual participants may pose challenges given that 15–17-year-olds will require parental consent. Previous research with alcohol use interventions reported lower rates of study enrolment and a bias towards participants with lower levels of alcohol use [67]. This was attributed to adolescents’ perception that their parents might learn about their alcohol use [63]. To address this challenge, parental consent is being sought after initial screening. Given that the inclusion criteria for study participation includes both depression and alcohol use, limited information on why the adolescent qualifies for the study will be disclosed. Further, retention of participants in a four-session intervention and through the lifespan of the study may pose some challenges. We have a comprehensive strategy to limit attrition (including reimbursement of transport costs) that has been used in other studies where we have obtained more than 80% follow-up rates [35].

In summary, this study has the potential to fill an important knowledge gap regarding promising trans-diagnostic counselling interventions for at-risk adolescents. Evidence generated by this study will be of direct relevance to current efforts to reform the public health system in South Africa and other LMICs where there is a focus on expanding access to mental health care to adolescents.

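### The 100 participants allow for attrition only, but each proposed primary outcome is analysed in an at-risk subset, so 70 measured is not secured for either one

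*Protocol article*

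**What the plan says.** Sample size considerations gives one rationale. It declines a power calculation ("As we are not testing effect sizes in this feasibility trial, a power calculation is not required"), cites a recommendation that "at least 70 measured subjects (35 per group) are required when estimating the SD for a continuous outcome", and concludes: "Therefore, we will recruit 100 participants (50 per group) to account for attrition". No attrition rate is stated. The only follow-up figure is in the Discussion, where the retention strategy "has been used in other studies where we have obtained more than 80% follow-up rates".

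Under Participants, an adolescent qualifies with a CES-D-10 score of 10 or more "and/or screen at moderate or severe risk for alcohol-related health problems, with a score ≥ 5" on the ASSIST-Y. A requirement of at least two heavy-drinking episodes in the last month follows after a semicolon.

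The analysis sets are narrower than the enrolled sample:
- Symptoms of depression: "This outcome is restricted to those with CES-D" of 10 or more at baseline.
- Alcohol severity: "This outcome is restricted to adolescents who report alcohol problems at baseline".
- Percent of heavy drinking days: its own section has no restriction, but Data analysis says: "We will create separate models for alcohol and depression and only include participants who screen at risk at baseline".

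Data analysis also says that the parameters for sizing a future main trial will be evaluated.

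**The concern.** The target of 70 is counted over everyone enrolled, while the proposed primary outcomes are analysed in subsets of unknown size. The step from 70 to 100 pays for one loss (drop-out) and not for the other (participants not at risk for that condition). A colleague who reads only the sample-size section would assume that each primary-outcome SD will rest on about 70 people. Informing a fully powered trial is part of the primary objectives, so the expected precision of those SDs should be stated for the sets in which they will be estimated.

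**Working it through.** **Inputs from the protocol.** Recruited: 100, allocated 1:1. Target measured: 70. Follow-up in earlier studies: more than 80%. Entry by either condition. Models restricted to those at risk.

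**Assumptions.** The share at risk for each condition is not given, so a range is used. Follow-up is taken to be the same in every subset. Everyone enrolled qualifies on at least one condition.

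**Step 1: the plan's own figure.** Recruits = 70 / (1 − d), where d is the loss. For d = 10, 15, 20 and 25% this gives 78, 83, 88 and 94. For d = 30% it gives 70 / 0.70 = 100. The stated 100 thus reproduces at an inferred 30% loss, and attrition then uses the whole margin.

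**Step 2: measured number per outcome** = 100 × share × follow-up.

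| Share at risk (assumed) | 70% follow-up | 80% follow-up | 90% follow-up |
|---|---|---|---|
| 50% | 35 | 40 | 45 |
| 60% | 42 | 48 | 54 |
| 70% | 49 | 56 | 63 |
| 80% | 56 | 64 | 72 |
| 90% | 63 | 72 | 81 |
| 100% | 70 | 80 | 90 |

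**Step 3: share needed for 70** = 0.70 / follow-up.
- 70% follow-up: 0.70 / 0.70 = 100%.
- 80% follow-up: 0.70 / 0.80 = 87.5%.
- 90% follow-up: 0.70 / 0.90 = 77.8%.

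**Step 4: overlap needed for both outcomes to reach 70.** Since everyone has at least one condition, share with both = depression share + alcohol share − 1. The minimum is 2 × 0.70 / follow-up − 1.
- 70% follow-up: 2 × 1.00 − 1 = 100%.
- 80% follow-up: 2 × 0.875 − 1 = 75%.
- 90% follow-up: 2 × 0.778 − 1 = 55.6%.

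The protocol gives no expected overlap and no quota or stratification by condition.

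**Step 5: effect on precision.** For a two-group pooled SD with normal data, df = n − 2, and the 95% limits are √(df/χ²(0.975)) and √(df/χ²(0.025)) times the estimate.
- n = 70: √(68/92.69) = 0.86 to √(68/47.09) = 1.20.
- n = 56: √(54/76.19) = 0.84 to √(54/35.59) = 1.23.
- n = 42: √(40/59.34) = 0.82 to √(40/24.43) = 1.28.

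The upper limit on the variance, to which a future sample size is proportional, is 68/47.09 = 1.44 times the estimate at n = 70 and 40/24.43 = 1.64 times at n = 42.

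**The case against.** A reader might infer that neither primary outcome is likely to reach 70. The documents do not support that. They give no case mix, and because everyone enters on at least one condition, a low share on one forces a high share on the other. An illustration uses the school-survey figures in the Discussion: 25% heavy episodic drinkers among lifetime drinkers and 56% at mental health risk. Assume independence, 50% lifetime drinking, and that these figures stand in for the entry criteria. Then alcohol risk is 0.25 × 0.50 = 0.125, the proportion eligible is 1 − 0.875 × 0.44 = 0.615, and the depression share is 0.56 / 0.615 = 91%. At 80% follow-up that gives about 73 measured for depression, but only about 16 for alcohol (0.125 / 0.615 = 20%). One outcome can reach 70 while the other falls well short.

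Other points on this side stand in part:
- If the heavy-drinking criterion binds everyone, the alcohol subset could approach the full sample. The punctuation leaves this open. The depression outcome would still be restricted.
- Heavy drinking days is restricted only through the models in Data analysis. The sentence there on parameters for the main trial names no subset.
- The 70 is a cited recommendation for a continuous outcome, not an explicit undertaking for each primary outcome. The secondary outcome sections state no at-risk restriction, so those outcomes can reach 70. Even so, the protocol uses the 70, with a therefore, as its whole case for 100.
- Clinical outcomes are secondary here, no progression criterion in Table 2 uses an SD, and whoever sizes the main trial will see the actual number per outcome. This limits the consequence but does not make the stated rationale fit the stated analysis.

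**Conclusion.** The point holds in a limited form. The sample-size rationale and the analysis restriction, both stated in the article, do not fit together: 100 recruits do not secure 70 measured for either proposed primary outcome. This is not a detail left to an analysis plan. Whether a given outcome falls short depends on a case mix that the protocol does not give. At the implied 30% loss it falls short at any share below 100%, at 80% follow-up at any share below 87.5%. Both outcomes reach 70 only if at least 75% of participants (80% follow-up) or about 56% (90% follow-up) have both conditions. The loss of precision is moderate: the upper 95% limit for the SD rises from 1.20 times the estimate at 70 to 1.23 at 56 and 1.28 at 42. The 42 combines an assumed 60% share with the inferred 30% loss, so it is not a forecast. Severity is minor to moderate. Nothing here invalidates the feasibility objectives or the progression criteria.

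**What to change.** Reword Sample size considerations in three respects:
1. Say that the 70 measured (35 per group) refers to the whole sample, and state the attrition rate assumed.
2. Give the expected number measured for each proposed primary outcome as 100 × share at risk × follow-up, over a range of assumed shares such as 50 to 90%. Say whether the heavy-drinking criterion applies to all participants, since the alcohol row depends on it.
3. Give the SD precision at those numbers, for example 95% limits of 0.86–1.20 times the estimate at 70, 0.84–1.23 at 56 and 0.82–1.28 at 42.

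In Data analysis, add that each outcome's SD will be reported with its own number and confidence interval. That is enough: which confidence limit a later trial is sized from is for that trial's protocol to choose.

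Enrolment should not be increased. The cost is a few sentences and one small table, and a less favourable statement of precision for the primary outcomes.

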### Data analysis

The quantitative outcomes of interest (see Table 2) will be summarized descriptively using appropriate summary statistics (mean and standard deviation for continuous outcomes and numbers and proportions for categorical outcomes) and presented graphically over time for both study arms.

We will explore clinical outcomes. In these exploratory analyses, we will calculate means and confidence intervals of clinical outcomes (both within- and between-study groups) and determine which outcomes are most sensitive to change. We will evaluate the parameters required to inform the sample size calculation for a future main trial. We will also assess change in clinical outcomes using an intention-to-treat analysis. Outcomes will be compared between intervention and control groups using linear regression models, adjusting for the baseline score of the given outcome. We will create separate models for alcohol and depression and only include participants who screen at risk at baseline. The two primary outcomes will be ascertained at three time-points for each participant. This repeated measure feature will be used to estimate the intervention effects and 95% confidence intervals for the two primary outcomes at 6 weeks and 3 months for the contrast between the intervention and comparison condition.

Qualitative data will be coded with NVivo and analyzed using the framework approach [56]. Transcripts of interviews will be read for emergent themes and then coded. Coding and analysis will continue iteratively. Two project staff will code the transcripts; they will meet after the first five transcripts, and thereafter after every 10 transcripts, to compare notes. Cohen’s Kappa will be used to measure inter-coder agreement. Following the Consolidated Criteria for Reporting Qualitative Studies (COREQ), we will document the process according to the 32-item checklist [57].

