At the enrolment visit that will take place at the South African Medical Research Council’s (SAMRC) clinical research site in Delft, the fieldworker will re-screen the participant to confirm study eligibility prior to obtaining written informed consent/assent to participate in the trial. Thereafter the fieldworker will administer the baseline assessment in either English, Afrikaans, or isiXhosa, the three official languages of the Western Cape province. The assessment includes socio-demographic information as well as information on mental health and behavioral problems, family relationships; and social support. All participants will then be matched with a trained ASPIRE counsellor to receive a counselling session. After counselling is completed, the trial manager will assign the participants to the intervention or comparison group. The counselling session will take place the same day as enrolment. A further three counselling appointments will be scheduled for adolescents allocated to the intervention group. These will be spaced at least a week apart from each other. Participants will have six weeks from enrolment to complete all four sessions, whereafter a participant will time out of the intervention. Irrespective of study arm, all participants will be asked to return for follow-up assessments at 6-week and 3-month post-enrolment. During these follow-up visits, a fieldworker will re-administer the baseline assessments. Participants will have 30 days from their scheduled appointment to complete these follow-up assessments before timing out of that appointment.

A random sample of approximately 30 adolescents who received the ASPIRE intervention will be recruited to participate in qualitative interviews to explore their perceptions of (1) intervention acceptability and suggestions for modification; (2) feasibility of study procedures; and (3) barriers and facilitators to participation and retention in counselling. These will take place after their final follow-up assessment. Counsellors delivering the intervention will also be interviewed to examine their experience of delivering the intervention and to identify any barriers and facilitators to intervention delivery. Transport or costs associated with transport required to attend study or counselling appointments will be provided or reimbursed. Participants will receive grocery vouchers for completing the baseline and follow-up assessments.

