### Randomization and blinding

Participants will be randomly allocated in a 1:1 ratio to either the intervention or comparison arm. The randomization sequence will be prepared by the data manager (using a computer programme) and allocation will be done by a trial manager. The fieldworkers will phone the trial manager when an individual is ready to be allocated, and the trial manager will inform the fieldworker about the participant’s allocation based on the randomization sequence. The fieldworker will then notify the participant about his/her allocation and associated activities. Investigators will be blind to the sequence generation. The trial manager will have no direct contact with participants, and all allocations will be concealed until the individual is assigned to a study arm. To reduce potential performance bias, allocations will only occur after the first counselling session has been completed. Fieldworkers will conduct the baseline and follow-up assessments, and trained counsellors will deliver the intervention. Fieldworkers conducting the follow-up assessments will be blinded to the randomization arm. Counsellors delivering the intervention and fieldworkers (serving as outcome assessors) will function independently of each other. Counsellors will not conduct any assessments, ensuring that these assessments remain independent from the counselling sessions.

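### The exploratory arm contrast takes no account of counsellors, although counsellors deliver sessions 2 to 4 in the ASPIRE arm only; the intervals may be too narrow, and the counsellor ICC is not named for main-trial planning

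*Protocol article*

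**What the plan says.** Randomisation is individual: "Participants will be randomly allocated in a 1:1 ratio to either the intervention or comparison arm". Before allocation, every participant has one counselling session: "All participants will then be matched with a trained ASPIRE counsellor to receive a counselling session". The Comparison arm section says that this session is the same in both arms. Under Participant recruitment and study procedures, and in Table 1, sessions 2 to 4 are for the intervention arm only.

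The Data analysis section names the model for the clinical outcomes: "Outcomes will be compared between intervention and control groups using linear regression models, adjusting for the baseline score of the given outcome". It calls these analyses exploratory, fits alcohol and depression separately, and restricts each model to participants at risk on that condition at baseline. The only dependence it mentions is repeated measurement of the same participant. The article mentions no counsellor term, counsellor clustering or ICC, and does not give the number of counsellors.

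On planning, the same section says: "We will evaluate the parameters required to inform the sample size calculation for a future main trial". It does not list those parameters. The Sample size considerations section names one quantity to be estimated, the SD: "at least 70 measured subjects (35 per group) are required when estimating the SD for a continuous outcome".

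**The concern.** Three of the four sessions, including all the problem-solving, coping and emotional-regulation content, are delivered by counsellors in one arm only. This is a partially nested design. If some counsellors get better results than others in those sessions, participants who share a counsellor have correlated outcomes. The ASPIRE mean then varies more than a regression with independent errors allows for.

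Two things are at stake. The lesser is the width of the exploratory 95% intervals. The greater is planning. A primary objective is to inform a fully powered trial, and the design effect grows with the number of participants per counsellor. A dependence that is modest here can be large in a main trial with heavier caseloads, and an SD alone does not reveal it.

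**Working it through.** **The plan's own figure.** 2 × 35 = 70 measured participants. The target is "we will recruit 100 participants (50 per group) to account for attrition", so the implied loss is 1 − 70/100 = 30%. The article states no attrition rate for this trial. At 20% loss, 70/0.80 = 87.5, or 88 participants. Counsellors play no part in this figure, and the present point does not alter it.

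**Inputs for the check.**
- From the article: 50 per arm, 1:1. The team's earlier studies are said to have done well on retention ("we have obtained more than 80% follow-up rates"); 80% of 50 is 40.
- Assumed: 36 to 40 analysed per arm, 3 to 6 counsellors, and ICC 0.02 to 0.10 for the variance that arises in sessions 2 to 4.

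**Formulas.** With m participants per counsellor, the design effect on the ASPIRE mean is DE = 1 + (m − 1) × ICC. The comparison arm has no such term, so the true variance of the arm difference is (1 + DE)/2 times what the regression assumes. Approximate coverage of the nominal 95% interval is 2Φ(1.96/√[(1 + DE)/2]) − 1. Coverage was also simulated, with 4,000 trials per setting.

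| Counsellors × participants | ICC | DE | Variance ratio | Coverage, formula | Coverage, simulated |
|---|---|---|---|---|---|
| 3 × 12 | 0.02 | 1.22 | 1.11 | 93.7% | 94.0% |
| 3 × 12 | 0.05 | 1.55 | 1.275 | 91.7% | 91.5% |
| 3 × 12 | 0.10 | 2.10 | 1.55 | 88.5% | 88.7% |
| 4 × 10 | 0.02 | 1.18 | 1.09 | 94.0% | 94.4% |
| 4 × 10 | 0.05 | 1.45 | 1.225 | 92.3% | 93.0% |
| 4 × 10 | 0.10 | 1.90 | 1.45 | 89.6% | 89.8% |
| 6 × 6 | 0.02 | 1.10 | 1.05 | 94.4% | 94.4% |
| 6 × 6 | 0.05 | 1.25 | 1.125 | 93.5% | 92.5% |
| 6 × 6 | 0.10 | 1.50 | 1.25 | 92.0% | 91.8% |

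**Smaller at-risk subsets.** Eligibility is by depression and/or alcohol, so either model may hold fewer participants. With 24 per arm and 4 to 6 counsellors, m is 6 to 4. Over ICC 0.02 to 0.10 the formula gives coverage of 94.4% to 92.0% with 4 counsellors and 94.7% to 93.2% with 6.

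**Session 1.** If the counsellor effect were wholly shared by the arms through session 1, and each counsellor's participants split evenly between arms, it would cancel. Simulated coverage is then 94.6% to 96.4% (50 per arm; 2, 4 or 6 counsellors; ICC 0.02 to 0.10).

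**What the SD contains.** With total variance 1, the expected sample variance in the ASPIRE arm is (n − DE)/(n − 1). For 3 × 12 at ICC 0.10 this is (36 − 2.10)/35 = 0.97. The observed SD therefore already holds nearly all the between-counsellor variance. It does not show how that variance splits between and within counsellors, and the design effect needs that split.

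**Main-trial illustration.** Assume a standardised difference of 0.3 and 80% power: 175 per arm, 350 in total with independence. At 20 participants per counsellor, the multiplier (1 + DE)/2 is 1.095, 1.475 or 1.95 at ICC 0.01, 0.05 or 0.10. The totals become 384, 518 and 684. None of these inputs is in the article.

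**The case against.** The strongest case on the other side has five parts.

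1. **Little depends on the contrast.** The protocol says "As we are not testing effect sizes in this feasibility trial, a power calculation is not required", calls the clinical analyses exploratory, and has no progression criterion in Table 2 that uses the arm difference or its interval. This stands, and it makes the interval issue low priority for this trial.

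2. **The article is condensed.** A counsellor effect may appear in an analysis plan that is not shown. This stands in part. The article does more than stay silent: it fixes the model, its covariate and the one source of correlation to be used, and as stated that treats participants as independent across counsellors.

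3. **The loss is conditional.** A reader might infer that the intervals are certainly too narrow. The documents do not support that. It needs counsellor variance specific to sessions 2 to 4 and fairly few counsellors, and the article gives neither figure. It also does not say whether one counsellor keeps a participant throughout. The competency ratings are no proof of outcome clustering: common training, weekly supervision and fidelity feedback aim to make delivery uniform. At ICC 0.02 the loss is negligible.

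4. **No main-trial size is set.** A reader might infer that the main trial is already being planned without counsellor variation, or that the SD leaves that variation out. Neither holds. The parameter list is open, the SD section justifies the size of the feasibility trial only, and the observed SD is a total SD. What can fairly be said is that the ICC is not named.

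5. **A counsellor model is costly with few counsellors.** With Satterthwaite degrees of freedom, (DE + 1)² / [DE²/(k − 1) + 1/(n − 1)] for k counsellors and n per arm, the settings in the table give about 4 to 16. Intervals come out 1.09 times (6 × 6, ICC 0.02) to 1.69 times (3 × 12, ICC 0.10) as wide as the naive ones. This stands, and it is a reason to make the counsellor model a sensitivity analysis and not a replacement.

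**Conclusion.** The point holds in a conditional form. The design is partially nested and the stated regression does not allow for it. If sessions 2 to 4 add counsellor-level variance, the 95% intervals will be too narrow: coverage is about 94% to 89% with 3 to 6 counsellors, ICC 0.02 to 0.10 and 36 to 40 analysed per arm, with less loss in smaller at-risk subsets. Any part of the counsellor effect shared through session 1 largely cancels. Counsellor number and ICC are assumptions throughout.

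For this trial's own decision the priority is low. The main value lies in main-trial planning, where the SD, the only design parameter named, cannot supply the design effect.

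**What to change.** - **Data collection:** record the counsellor for each session. Counsellors already write notes after every session, so this is one extra variable.
- **Data analysis:** keep the stated regression and report a partially nested sensitivity analysis beside it, with a counsellor effect in the ASPIRE arm and a small-sample correction. If there are too few counsellors to fit this, show the intervals inflated over an assumed ICC range.
- **Main-trial parameters:** name the counsellor ICC among them and report it with its interval. State that the main-trial sample size will be shown over an assumed ICC range, because this trial's own estimate will be imprecise.

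Design, recruitment and care do not change. The cost is wider intervals in the sensitivity analysis, possibly clearly wider with few counsellors, and an ICC estimate that cannot be used alone.
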